## Abstract

**Background:**

Nicotine replacement therapy (NRT) and short messaging service (SMS)-based tobacco cessation interventions have demonstrated effectiveness in reducing tobacco use in many populations, but evidence is needed on which tailored treatments are most efficacious in meeting the complex medical and psychosocial factors confronting people living with HIV (PLWH) in sub-Saharan Africa (SSA). This paper describes the protocol of a study to test the efficacy of both NRT and a tailored SMS-based tobacco use cessation intervention among PLWH in Uganda and Zambia.

**Methods:**

In a randomized controlled trial, 800 adult PLWH who use tobacco will be recruited by health care professionals at HIV treatment centers where they are receiving care. Participants will be randomized to one of the four study arms: (1) standard of care [SOC; brief clinician advice to quit combined with HIV education and information aimed at encouraging HIV treatment adherence (with no mention of tobacco) delivered via text messages]; (2) SOC + 12 weeks of NRT; (3) SOC + 6 weeks of SMS text messages to support quitting tobacco use (SMS); or (4) SOC + NRT + SMS. Participants will receive a cell phone and solar panel with power bank for charging the phone. The main outcome is cessation of tobacco use by study participants verified by urinary cotinine (< 15 ng/mL) at 6 months post-enrollment. As a secondary tobacco use outcome, we will measure 7-day point-prevalence abstinence (7 consecutive days of no tobacco use) measured by self-report and biochemically-verified at 4 weeks, 8 weeks, and 3 months post enrollment.

**Discussion:**

Our study will provide insight into the efficacy, feasibility and applicability of delivering tobacco cessation interventions through health care professionals combined with tailored tobacco cessation SMS text messaging in two countries with different tobacco use patterns, policy environments, and health care resources and provide needed information to providers and policymakers looking for cost-effective tobacco cessation interventions. The previously tested SMS-platform to be used in our study is uniquely positioned to be scaled in low- and middle-income countries worldwide, in which case evidence of even modest success in reducing the prevalence of tobacco consumption among PLWH could confer enormous health and economic benefits.

*Trial registration:* ClinicalTrials.gov Identifier NCT05487807. Registered August 4, 2022, https://clinicaltrials.gov/ct2/show/record/NCT05487807

## Background

AIDS-related morbidity and mortality among people living with HIV (PLWH) have decreased with the introduction of combination antiretroviral therapy (ART), but HIV remains among the world’s deadliest infectious diseases. In 2021, an estimated 650,000 people died from AIDS-related illnesses, with 51% of new HIV infections occurring in sub-Saharan Africa (SSA) [1]. Both Uganda and Zambia have significant HIV burdens, with Zambia having about double the prevalence of Uganda (10.8 vs. 5.2, respectively) [2]. Tobacco use among PLWH contributes substantially to the HIV burden, with an estimated 24% of AIDS-related deaths attributable to smoking [3]. Tobacco use among PLWH contributes to increased rate of progression to AIDS, poorer outcomes in HIV-associated opportunistic infections, increased risk of developing chronic diseases, and poorer adherence and response to ART [4–6]. Notably, PLWH in SSA have high rates of tuberculosis, which is exacerbated by smoking, making this region a particularly critical one for tobacco cessation efforts [7]. Similar to elsewhere, having HIV has been found to be associated with a greater likelihood of tobacco use in SSA with adjustment for demographic, socioeconomic, and sexual risk factors [8–10]. In Uganda, a study from 2014, which used salivary cotinine to identify tobacco users, found the prevalence of tobacco use among PLWH was twice that of the local background population (20% vs 10%) [11]. In Zambia, the 2018 Demographic and Health Survey found that the prevalence of tobacco use was higher among PLWH than non-PLWH for both women (4.4% vs. 2.4%) and men (27.8% vs. 18.7%) [12].

Research on tobacco cessation in PLWH indicates unique challenges, including higher rates of depressive symptoms and mental health issues, greater use of alcohol and illegal substances, lack of awareness about tobacco’s effects on HIV treatment, lower interest in quitting, and lower adherence to treatments [5, 13–17]. However, evidence suggests that HIV-positive smokers are receptive to quitting smoking and intention to quit smoking may increase upon the onset of HIV or an advancement in disease progression [18]. Tailored treatment approaches that meet the complex medical and psychosocial factors PLWH face, including education on how tobacco use impacts HIV prognosis, addressing depressive symptoms, and connecting patients to community support services, can improve outcomes among PLWH [19–22]. The medical infrastructure built around HIV treatment, including regular contact between HIV patients and health professionals, provides natural entry points for such sustained tobacco use cessation interventions. Prior rigorous research underscores the feasibility of integration of tobacco cessation services in resource-constrained HIV treatment centers [23–25].

There are multiple evidence-based cessation strategies that have been widely tested and found effective within the general population in high-income countries, including clinic-based tobacco cessation interventions such as physician-delivered tobacco cessation advice [26], group therapy [27], individual counseling [28], self-help materials [29], telephone counseling [30], and nicotine replacement therapy [31]. A handful of studies have been conducted in low- and middle-income countries (LMICs) [32] and in SSA focused on NRT and psychotherapy with mixed results [33]. A Cochrane Systematic Review also concluded that automated short text messaging (SMS) interventions were more effective than minimal smoking cessation support and text messaging added to other smoking cessation interventions was more effective than the other smoking cessation interventions alone [34]. A separate systematic review also concluded that smoking cessation support delivered by SMS increases quitting rates and was more effective at supporting cessation than smart phone smoking cessation treatment applications [35].

Recognizing the widespread use of mobile phones across socio-demographic groups in LMICs [36] and the potential of phones-based interventions to overcome communication and health care access barriers in LMICs [37, 38], WHO and the International Telecommunications Union launched the *Be He@lthy, Be Mobile* program in 2014 [39]. The program supports national scale-up and sustainability of mHealth programs related to non-communicable diseases, including a SMS-based program to help tobacco users quit [40]. To date, the tobacco cessation platform has been implemented in over 10 countries with positive results in regard to efficacy and acceptability [41]. For example, in India, the SMS-cessation platform enrolled over 1 million users within a year and achieved 19% successful quit rate at 4–6 months after completion of the program [42]. In 2017, WHO funded the Center for Tobacco Control in Africa to adapt and test the platform in Uganda among tuberculosis patients [43]. The resulting program, entitled Quit4Life, has been adapted, translated and is currently being tested in 7 districts in Uganda. While these study data are not yet published, numerous mHealth research studies conducted in Uganda and Zambia in other disease areas have found phone-based interventions are feasible, inexpensive, and viewed favorably by patients [44–46].

### The present study

While NRT and SMS-based tobacco cessation interventions have demonstrated effectiveness in reducing tobacco use in many populations, evidence is needed on which tailored treatments are most efficacious in meeting the complex medical and psychosocial factors confronting PLWH in SSA. We approach this gap with the first randomized controlled trial (RCT) to test the efficacy of both NRT and a tailored SMS-based tobacco use cessation intervention among PLWH in Uganda and Zambia. Our study will provide insight into the efficacy, feasibility and applicability of delivering tobacco cessation interventions through health care professionals at HIV treatment centers in two countries with different tobacco use patterns, policy environments, and health care resources and provide needed information to providers and policymakers looking for cost-effective tobacco cessation interventions. The previously tested SMS-platform to be used in our study is uniquely positioned to be scaled in LMICs worldwide, in which case evidence of even modest success in reducing the prevalence of tobacco consumption among PLWH could confer enormous health and economic benefits.

**Fig. 1 Fig1:**
[figure not shown]
Randomized controlled study trial flow

A core aim of this research is to generate data to inform the rapid scale-up of previously tested strategies, including mobile technology, for PWLH in LMICs. To achieve that, our study design tests interventions across and between diverse tobacco use patterns, policy environments, and health resources. While Uganda and Zambia are both SSA countries, they have differing HIV prevalence rates, tobacco use patterns, and tobacco control policy environments. For example, in 2015 Uganda passed comprehensive tobacco control legislation, while Zambia has struggled to push their legislation through parliament [47]. In site selection, we have considered regional prevalence of HIV, tobacco use patterns, and client load at HIV treatment centers. To meet the aims of the RCT, we chose two regions in each country with the highest tobacco use, allowing us to confidently recruit a sample size to more easily detect the desired effect size in case it exists.

### Participants and recruitment

Individuals will be eligible for the study if they are HIV + , use tobacco according to the definition below, are aged 18 years or older, and are receiving continuous HIV care from a treatment facility. Individuals will be ineligible for study participation if they: are currently pregnant or breastfeeding (or planning to do so in the next 6 months); have a physical or cognitive condition that would prevent them from study participation; or are illiterate in both English and the local language.

Participants will be recruited by health care professionals at HIV treatment centers where they are receiving care based on their HIV + status. Eligibility screening for the RCT will include completion of a questionnaire about current and past tobacco use, including intention to quit and/or past quit attempts. We will inquire about both combustible and non-combustible tobacco use, as there is a substantial amount of smokeless tobacco use (e.g., rolled, sniffed) in the districts that are the geographic focus of the study. We anticipate that e-cigarette use among our sample population will be rare. Tobacco use status will be biologically verified at baseline using urine cotinine dipsticks [48, 49]. The cotinine cut-off to detect current tobacco use will be > 15 ng/mL, as validated among African populations [50–52]. Although data are scarce, we suspect a substantial number of irregular smokers within the study catchment areas and level of dependence may also vary from what is typical in other countries [18, 53]. Consequently, typical measures used to identify participants for smoking cessation interventions, such as 10 cigarettes a day, may be inappropriate for this study. Therefore, in addition to self-reported and biologically-verified daily tobacco use, we will include a threshold level of nicotine dependence. We will train local recruiters to administer the Fagerstrom Test for Nicotine Dependence (FTND) [54] for both smoking and smokeless tobacco use [55]; individuals must have a score of 4 (the average score for a daily smoker [56]) or above to participate in the study.

Verbal consent will be obtained for completing the eligibility screener and eligible individuals will then be asked to provide written informed consent for RCT participation. Research staff will read the consent form aloud to the individual, who will follow along from their own copy (which will be available in both English and the local language), and answer any questions that the individual might have before signing the form. A Certificate of Confidentiality has been obtained for this project.

### Intervention setting

To facilitate the identification of PLWH that leverage existing HIV care infrastructure, we will carry out the study at HIV treatment centers in 16 sites located in two remote districts in Uganda and Zambia each [57–60]. In Uganda, the two districts selected are Arua located in the northern West-Nile region, and Moroto located in the northeast Karamoja region. West-Nile (Arua) is an agrarian society, whereas Karamoja region (Moroto) is mainly a nomadic society with strong social cultural ties. In Zambia, two districts in two provinces were selected: Mongu in the Western Province and Chipata in the Eastern Province. Mongu is in the western part and Chipata is in the eastern part of the country, both approximately 600 kms from Lusaka, the capital city. The predominant livelihood activity for the people in the Mongu study site is fishing in the flood planes of the Zambezi River, while on the other hand, people in the Chipata study sites are small scale farmers. To this extent, the two sites are different. However, Mongu (Western) and Chipata (Eastern) are similar in the sense that they are the highest two sites in Zambia in terms of HIV prevalence rates.

### SMS delivery

At enrollment, all participants will receive a project-provided mobile phone and a solar panel for charging the phone, as well as instruction on how to use the phone (including the use of security settings to alleviate privacy concerns). The phones will be basic text-based phones with no study identifiers. Such phones are very prevalent throughout the study areas and previous research with similar basic mobile phones has shown that they are effective for text message delivery and user friendly [61–63]. While mobile phone coverage is widespread in Uganda and Zambia, PLWH in our target communities represent among the most vulnerable individuals and thus least likely to have a personal phone; as such, due to the efficacy aims of this study providing phones will facilitate enrollment and expedite our results. 

The SMS text libraries will differ across intervention conditions. Participants in the SOC and SOC + NRT arms will receive 22 text messages focused specifically on HIV education and importance of adhering to HIV treatment regimen. These texts will not include an interactive component (e.g., no check-ins with participant; participant cannot request additional information). The HIV text messages were adapted from Uganda AIDS Commission (UAC) HIV messages library [64]. Participants in the SOC + SMS arm will receive the 22 SOC text messages, as well as up to 225 text messages focused on tobacco cessation: 164 standard text messages, 33 prompted questions (e.g., asking if they have quit), and 28 possible requested information texts. Table 1 provides the flow of when participants will receive the cessation messages throughout the program. These messages were either adapted from SmokefreeTXT or developed based on stakeholder feedback during the formative phase of this project, as described below. Finally, participants in the SOC + NRT + SMS arm receive the 22 SOC text messages, the up to 225 text messages focused on tobacco cessation, and up to 11 additional text focused on use of the nicotine patch (i.e., 5 standard text messages, 5 prompted questions, and 1 possible requested information text).

**Table 1 Tab1:** Quit4Life + tobacco cessation-related text message flow (does not include SOC- or NRT-related texts)

Timepoint	Number of texts per day
Enrollment texts (Day -15)	12
Pre-quit texts (Days -14 to -1)	
14 to 8 days before quit day	2 texts
7 to 1 day before quit day	3 texts
Quit day texts (Day 0)	
Quit day	6 texts
Early post-quit texts (Days 1 to 14)	
1 day post-quit	3 texts
2–6 days post-quit	4 texts
7 day post-quit	5 texts
8–14 days post-quit	4 texts
Later post-quit texts (Days 15 to 42)	
15 to 28 days post-quit	2 to 3 texts
29 to 42 days post-quit	2 texts
Tobacco use check-ins	
Days 72, 132, and 222	1 text

### Description of intervention components

*Standard of Care (SOC)*. Participants in all four arms will receive the current minimum standard of care for tobacco cessation among PLWH in the study regions: brief clinician advice to quit delivered by staff at the HIV treatment center, combined with HIV education and information aimed at encouraging HIV treatment adherence (with no mention of tobacco) which will be delivered in this study via text messages.

#### Nicotine Replacement Therapy (NRT)

Participants in two of the four conditions (SOC + NRT; SOC + NRT + SMS) will receive up to a 12-week supply of nicotine patches, and clinician-delivered instructions on how to use the patch that follow package insert guidelines. The instructions will also include information on potential side effects of patch use. Dosing instructions will be tailored based on participants’ daily amount of tobacco use.

#### *Quit4Life* + *SMS Program (SMS)*

We followed World Health Organization recommendations for developing an mTobaccoCessation program for PLWH in Uganda and Zambia [39]. We first selected an existing SMS program that was publically available, evidence-based, and had been adapted for use in several countries outside the U.S.: SmokefreeTXT (http://www.smokefree.gov) [65]. In its original form, SmokefreeTXT is comprised of 125 standard text messages that are delivered over a 6-week period. These core messages focus on cessation strategies and support. In addition, there are periodic check-in texts to determine if participants are still using tobacco, as well as a pool of “on demand” texts that participants can receive to help them deal with cravings (text CRAVE), negative moods (text MOOD), or slips (text SLIP) during the quitting process. After selecting SmokefreeTXT for adaptation, we engaged in a formative phase of the project to obtain input from key stakeholders on what needed to be modified. Specifically, we conducted focus group discussions in Uganda and Zambia with health care providers (4 groups, 2 per country) and PLWH who used tobacco (8 groups, 4 per country) specifically for the purposes of adapting SmokefreeTXT for our target population [66]. Members of our research team from Uganda and Zambia, with combined expertise in tobacco cessation and HIV, also provided input on the adaptation process and resulting text library throughout the process.

SmokefreeTXT was adapted in four main respects: (a) modified existing texts to refer to tobacco use, rather than smoking specifically; (b) if possible, modified existing texts so that content was more appropriate and applicable to the local context in Uganda and Zambia; (c) deleted existing texts that could not be reasonably adapted to the local context; and d) added new texts to reflect content specifically tailored to PLWH in Uganda and Zambia that emerged from the formative research. Table 2 shows examples of additional domains that were added to the adapted SmokefreeTXT text library (e.g., basic education about health effects of tobacco use; information on HIV-related effects of tobacco use and quitting; socioemotional issues related to HIV-status that affect quitting; use of tobacco to decrease hunger; community norms that support tobacco use).

**Table 2 Tab2:** Examples of domains added to SmokefreeTXT based on formative research

Domain	Example text(s)
Basic education about health effects of tobacco use	Whether smoked, chewed, rolled, or sniffed, tobacco contains nicotine. Tobacco is very addictive. When you quit you will break your addiction
Information on HIV-related effects of tobacco use and quitting	Using tobacco will not improve your CD4 count. In fact, tobacco use is associated with a poorer response to HIV treatment
Alcohol use is widespread and a trigger for tobacco use	Drinking alcohol makes it more difficult to quit tobacco. For the next few days avoid alcohol and see if that helps reduce tobacco use
Socioemotional issues related to HIV-status such as boredom/idleness, isolation, loneliness	Think of healthy ways to deal with stress & boredom instead of using tobacco. Engage in a hobby or visit a friend to keep yourself busy Loneliness can make quitting hard, but tobacco-free is the way to go. Reach out to a trusted friend to ask for their company & support
Tobacco is used to decrease hunger	Using tobacco may decrease your hunger, but it harms your body and can result in sickness and early death
Community norms support tobacco use (e.g., use is widespread and not considered harmful; not using is a sign of weakness or disrespect; using is linked to friendships; women often hide their tobacco use)	Some might say that not using tobacco shows weakness or disrespect. That’s not true. Quitting shows others that you can do the hard work to improve your health Your community may not be concerned about tobacco, but you now know how harmful it can be. Stay strong for you and your health Even when there is a lot of tobacco around you, it doesn’t mean that it is safe for you. Continue staying tobacco-free Tobacco use will not improve your social status. It affects your health & the health of those around you. Continue staying tobacco-free If you hide your tobacco use, it might help to tell a trusted friend why you are quitting and how they can support you
Religious guidance may help quitting	Some people get support for quitting by praying to God for guidance, support and strength to overcome tobacco. Try it if you think it will work for you

### Randomization and blinding

Prior to initiation of the trial, a reputable media company/agency not associated with implementation of the trial will be contracted to be responsible for: i) generating a randomization scheme/schedule using serial numbers from 1 through 400 for each country site using an appropriate STATA code; ii) randomly assigning enrolled participants to the study arms; and iii) sending the respective SMS messages per the assigned study arm to the participants. The media company/agency will keep the generated randomization schedule and manage the randomization of participants. When a participant is enrolled at any of the study enrollment sites, they will be assigned the next serial number which also corresponds to a telephone number. The media company/agency not associated with implementation of the trial will immediately be notified, who will then assign the study arm to the participant in a sequential order of enrollment per the randomization schedule. The agency will subsequently start sending the respective SMS messages to the participants per the study arm assigned. This way the participants, the clinic staff, and the study team members including the investigators will be blinded to the allocation of participants to any of the study arms. However, since the participants will interact with the clinic staff every time they come for treatment at the health facilities, it is possible that they may share with the staff the messages they have received; as such, the staff may be able to determine which study arm the participant was assigned. Therefore, blinding is only assured up to the time when participants begin receiving the study messages.

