### Project monitoring and evaluation

Participants will receive prompts (close-ended questions that require a yes or no or numeric answers) on their phones periodically and at 6 months follow up to collect data about the study’s acceptability, feasibility, and impact. A subset of participants (*N* = 50) will be contacted by phone to provide more detailed feedback on their experience in the study. We will also collect feedback from participating clinic staff on the study through interviews (*n* = 30, 15 in each country) and focus groups (*n* = 4, 2 in each country). Key issues of concern with the clinic staff include ease of use and maintenance of the tablets that they will be asked to use for data collection, time it took to provide brief advice to quit and/or prescribe NRT and/or enroll a patient in the SMS program, acceptability of the program among patients, and whether providers felt the program improved their overall HIV treatment approach. We will track enrollment and retention trends and investigate any data inconsistencies that may reflect poor performance or deviations from the study procedures.

In addition, there will be an independent Data Safety and Monitoring Board (DSMB) composed of a clinician who is a specialist in HIV, a biostatistician, an expert in interventions studies and a community representative. The DSMB will monitor the safety of the participants, but also ensure that the study is conducted according to the protocol and will have access to the results on a regular basis so that they can take a decision at the earliest possible time when necessary. Specifically, the functions of the DSMB will be to review the research protocol, review the plans for data safety and monitoring, evaluate the progress of the intervention trial, review the data quality and timeliness as well as the accrual and retention. Other functions will include participants’ risk versus benefit and the performance of the trial sites.

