### Analytic Plan

#### Data management

Data will be collected at enrollment and at follow up appointments by trained clinic staff through a mobile-based application, REDCap (Research Electronic Data Capture), loaded onto a password protected tablet [67]. Data will be uploaded to the cloud daily through secure internet connections at the clinic sites to a REDCap webserver guarded by multiple firewall and intrusion detection systems. All electronic connections to the REDCap environment are encrypted. The data manager at the Center for Tobacco Control in Africa (CTCA) central coordination office will be responsible for downloading the data off the cloud into a secure MySQL database server behind the Makerere University firewall. REDCap implements authentication to validate the identity of end-users that log in to the system. The data manager at the CTCA central coordination office will be responsible for checking the accuracy and completeness of the data before entry into the database and following up with the relevant field team if any inconsistencies or problems are detected. Data will also be received from an independent media agency engaged by the study which contains a robust analytics framework to analyze the data collected, including how often participants receive and respond to prompts. The application interface allows for outside applications to interact with the data to carry out additional analyses. All data will be cleaned for final analysis by the CTCA data manager after it has been received.

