#### Measures

The primary tobacco use outcome for this efficacy trial is the proportion of study participants that have prolonged abstinence (i.e., no tobacco use from the target quit date through follow-up) at 3 and 6 months post enrollment measured by self-report and biochemically-verified as recommended by the Society for Research on Nicotine and Tobacco [69]. As a secondary tobacco use outcome we will measure 7-day point-prevalence abstinence (7 consecutive days of no tobacco use) measured by self-report and biochemically-verified at 4 weeks, 8 weeks, and 3 months post enrollment. The biomarker being assessed is urinary cotinine (< 15 ng/mL). We will also assess self-reported tobacco quit attempts and changes in tobacco use at 4 weeks, 8 weeks, and 3 months post enrollment. Finally, for those receiving nicotine patches, we will assess nicotine patch adherence at 4 weeks, 8 weeks, and 3 months post enrollment. Patch adherence will be assessed as the number of days the participant used a patch over the prior 4 week period, with adherence defined as using > 6 patches a week [70]. Self-reported patch use will be verified by a health worker who will conduct a patch count.

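### The blinding statement does not fit the nicotine-patch factor, which is open to participants and clinic staff whatever happens with the text messages

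*Protocol article*

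**What the plan says.** The Randomization and blinding section gives an outside media agency the schedule, the assignment of arms and the sending of texts. From this it concludes that "the participants, the clinic staff, and the study team members including the investigators will be blinded to the allocation of participants", for every arm. It then allows one exception: when participants attend the clinic, "it is possible that they may share with the staff the messages they have received", so that "blinding is only assured up to the time when participants begin receiving the study messages". Patches do not appear in this section.

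Elsewhere the protocol article says:

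- Nicotine Replacement Therapy (NRT): participants in SOC + NRT and SOC + NRT + SMS "will receive up to a 12-week supply of nicotine patches, and clinician-delivered instructions on how to use the patch". No placebo patch is described for the other two arms.
- Project monitoring and evaluation: clinic staff will be asked about the "time it took to provide brief advice to quit and/or prescribe NRT and/or enroll a patient in the SMS program", and about the tablets they use for data collection.
- Data management: "Data will be collected at enrollment and at follow up appointments by trained clinic staff".
- Measures: "Self-reported patch use will be verified by a health worker who will conduct a patch count". The same section defines the primary outcome as prolonged abstinence by self-report with biochemical verification. It lists quit attempts and change in tobacco use without any verification.

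**The concern.** The blinding described rests on an agency that controls text messages. That can hide which texts a participant gets. It cannot hide a patch. A clinician who prescribes patches and explains their use knows who has been assigned to them, and participants know whether they were given any.

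Two things are at stake. First, a reader judging risk of bias would credit the NRT comparison with blinding that the design does not provide. Second, follow-up data are taken by clinic staff, and part of every abstinence outcome is the participant's own account. Where the person asking and the person answering both know the treatment, the account may be influenced by that knowledge.

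**Working it through.** No formula applies. The check sets the sections side by side.

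**Step 1: what each arm receives** (SMS delivery and NRT sections)

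| Arm | Texts | Patches |
|---|---|---|
| 1. SOC | 22 HIV texts | no |
| 2. SOC + NRT | the same 22 HIV texts | yes |
| 3. SOC + SMS | 22 + up to 225 = up to 247 | no |
| 4. SOC + NRT + SMS | 22 + up to 225 + up to 11 = up to 258 | yes |

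**Step 2: does the message exception cover the patches?** Arms 1 and 2 receive the same texts. A participant in arm 2 could show staff every message and still not be distinguishable from one in arm 1. What separates these arms is the patch, which the blinding section does not consider. The exception therefore misses the NRT factor.

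**Step 3: is the patch a possible leak or a certain one?** The protocol treats shared messages as something that might happen. For patches, disclosure is part of delivering the treatment: staff prescribe, instruct, and later have patches counted. Staff must be told who is to receive them, although the section describes no route by which they are told. With no placebo described, not receiving a patch is as informative as receiving one.

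**Step 4: how many participants?** With 200 planned per arm, 2 × 200 = 400 receive patches and 2 × 200 = 400 do not. The NRT half of the allocation is visible for all 800.

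**Step 5: is the SMS half hidden from staff?** It may be, since the agency sends the texts. But the Project monitoring and evaluation section counts enrolling patients in the SMS program among the staff tasks. Staff blinding to SMS cannot be taken as assured either.

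**Step 6: which outcomes are exposed?** (Measures section)

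- Prolonged abstinence at 3 and 6 months: self-report plus verification. A reading at a visit cannot confirm abstinence all the way back to the quit date, so that part depends on self-report.
- 7-day abstinence at 4 weeks, 8 weeks and 3 months: self-report plus verification.
- Quit attempts and change in use at the same three visits: no verification is described, so these are fully exposed.

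**The case against.** The strongest reply is that the protocol already disclaims blinding for the period that matters. The agency is notified at enrolment and starts the texts after assigning the arm. All outcome visits, from 4 weeks on, come later, and the section says blinding is not assured once texts begin. No reader is told that outcome assessors are blind. This stands in part: the protocol makes no claim of blinded assessment. It does not rescue the statement, because the reason given (shared messages) does not apply to patches, and a certainty is presented as a possibility.

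A second reply is that abstinence needs urinary cotinine below 15 ng/mL, so over-reporting alone does not make a quitter. This also stands and limits the harm. It leaves use between visits, and the unverified outcomes.

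A third is that form order and coding of arms usually belong in the full protocol, procedures or analysis plan. Their absence here is not counted as a fault. They are offered as safeguards once the NRT factor is acknowledged as open.

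Some stronger readings are tempting but not supported:

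- That no blinding or concealment exists at all. Concealment before assignment is described, and nothing shows that the central investigators are unblinded.
- That the 6-month cotinine result is the only objective element. Verification is also planned at 4 weeks, 8 weeks and 3 months.
- That the bias must favour the active arms. This is plausible, but the document gives no basis for its direction or size. The remark about hesitancy to report tobacco use concerns recruitment.
- That the individual who dispenses a participant's patches also records that participant's outcomes. The text refers to clinic staff and health workers as groups.

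**Conclusion.** The blinding statement is wrong as written for the NRT factor. Participants and the clinic staff who handle patches know the NRT allocation in all four arms, whether or not any message is shared. Staff blinding to the SMS factor is not assured. The effect on the verified abstinence outcomes is limited by cotinine but not removed. Quit attempts and change in use have no such protection. The size of any bias cannot be computed from the document.

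The conclusion rests on one inference, that patches are open because no placebo is described. The article also does not say when patches are handed out relative to the first text, so the moment at which NRT status becomes known cannot be dated. Neither point alters the contradiction. The correction is worth making, but it does not threaten the randomization or the primary analysis.

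**What to change.** Reconcile the Randomization and blinding section with the NRT, Project monitoring and evaluation, Data management and Measures sections. State that:

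1. allocation is concealed until assignment;
2. NRT is open-label to participants and clinic staff;
3. blinding of clinic staff to the SMS factor is not assured, since they are described as enrolling patients in that program;
4. any role that does stay blinded is named.

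Then add three safeguards:

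- At each visit with biochemical verification, read the cotinine test and enter the result before the tobacco-use interview and before any patch question.
- Keep arms coded for the data manager and analyst until the primary outcome data are locked. Patch-adherence fields and the agency's message logs reveal the arm, so they should be held apart until then.
- Report outcomes based on self-report alone as unblinded.

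The cost is a text correction, a fixed order of items on the visit forms, and separate storage of two data sets. No visit, staff post or treatment changes.
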